#### Secondary outcome measures

Secondary outcome measures will include:change in grip strength, which will be measured by the JAMAR® hand dynamometer (average of 3 trials in kg);change in Box and Block test, which will be used to evaluate manual dexterity by counting the number of blocks that can be moved from one compartment to another in 60 s [43];change in Motor Activity Log, which will assess participants’ self-reported level and quality of use of the affected arm in activities of daily living (ADL) [44] and;change in active and passive ranges of motion in shoulder flexion, elbow flexion and wrist extension, which will be assessed with a goniometer.

Along with the FMA, these variables were chosen to ensure that the most severely affected participants would be able to perform to some extent the required tasks, knowing that individuals without MEPs often present limited voluntary movement at the affected upper limb.

### Sample size and power calculations

A priori power analysis was performed in G*Power 3.1.9.2, using a two-tailed independent samples t-test having an alpha level of 0.05, to calculate the sample size required in this study. By stratifying participants based on their MEP amplitude to provide an appropriate dosage of training, we expect all participants within the three MEP strata to benefit from the 4-week tailored strength training program. The sample size was thus calculated based on the expected difference in motor function gains between the tDCS real and the tDCS sham groups. Based on the results of studies having used repetitive application of tDCS in chronic stroke survivors, we expect an 8-point gain in FMA for the tDCS real group [56]. Furthermore, preliminary results based on this study showed a 7-point gain on the FMA scale after 4 weeks of strength training for participants presenting pre-training MEPs. Therefore, we estimate that the tDCS sham group (including participants with and without MEP) will show at least a 6-point gain on the FMA scale, exceeding the 5-point gain minimal detectable change (MDC) of this scale [57]. Thus, with an estimated average difference in FMA gain between both groups of 2 points (SD = 3), with an effect size of 0.66 and a power of 85%, we calculated that a total of 84 participants will be needed to detect differences between groups. However, presuming an attrition rate of 20%, a total of 105 participants will be recruited for the purpose of this study.

### Statistical analysis

Descriptive statistics will be used to characterize the sample. We will verify if, at the beginning, the two tDCS groups will be comparable by using independent t-tests or Chi-squared tests, depending on the nature of the variables. To evaluate the impact of tailored exercises based on MEP stratification on changes in FMA and MEP measures, as well as the impact of tDCS on enhancement of training response, a two-way 3X2 ANOVA [MEP strata (three levels) and type of tDCS (2 levels)] will be used. The significance level will be set at 0.05. If an interaction is noted, paired *t*-tests will be used to locate any significant differences in each stratum with a Bonferroni correction for multiple tests (adjusted *p*-value of 0.02).

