## Methods

### Study design and setting

This is a multi-centre, randomised controlled trial (RCT) study. Figure 1 illustrates the flow diagram of the study from recruitment and screening for eligible participants to post-training outcome assessments. The RCT takes place in Canada and involves three recruiting sites in two provinces (Québec: Montréal, Sherbrooke; Ontario: Ottawa). The study is ongoing and is currently during subject recruitment phase (May 2017 till present).

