#### Randomisation and blinding

According to the amplitude of their TMS-induced MEP responses, three levels of stratification will be used, which are adapted from Milot et al. [22]: 1) no detectable MEPs (< 50 μV); 2) detectable MEPs (50-120 μV) and 3) clearly detectable MEPs (> 120 μV). Within each stratum, participants will be further randomly allocated into two tDCS groups: 1) tDCS real group and 2) tDCS sham group. Participants will be randomly assigned to either the tDCS real group or the tDCS sham group with a 1:1 allocation. Randomisation allocation will be generated by a computer using a blocked randomisation with variable block sizes of 2 and 4. The participants, the evaluators, involved in the clinical and neurophysiological evaluations, the research staff enrolling participants and the data analysts will be blinded to the tDCS group assignment.

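### The ANOVA of FMA change omits baseline FMA, which is collected in everyone; adding it would bring a modest gain in precision at almost no cost.

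*Protocol article*

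**What the plan says.** All references are to the protocol article.

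- **Outcome.** Primary outcome measures defines the clinical primary outcome as change in FMA, with 66 as the normal score. Assessment period and Clinical evaluation show that FMA is measured before and after training.
- **Model.** Statistical analysis fixes the analysis of these changes: "a two-way 3X2 ANOVA [MEP strata (three levels) and type of tDCS (2 levels)] will be used". No covariate is named.
- **Baseline comparability.** The same section states: "We will verify if, at the beginning, the two tDCS groups will be comparable by using independent t-tests or Chi-squared tests". It attaches no consequence to the result of these tests.
- **Allocation.** Randomisation and blinding allocates within MEP strata, to "either the tDCS real group or the tDCS sham group with a 1:1 allocation". Study design and setting says the trial "involves three recruiting sites in two provinces".
- **Eligibility.** Inclusion/exclusion criteria sets no lower or upper limit on FMA.
- **Planning figures.** Sample size and power calculations plans on a t-test of FMA gain between the real and sham groups.

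**The concern.** A change score is fully efficient only if change is unrelated to the starting value. Here there is reason to expect some relation. The plan expects an 8-point gain with real tDCS, and on a scale ending at 66 nobody who starts above 66 − 8 = 58 can achieve it. Nothing in the eligibility criteria excludes such people. Regression to the mean works in the same direction.

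If change depends on baseline within a stratum, leaving baseline out has two consequences. The residual variance is larger than it needs to be, and a chance baseline difference between the arms is only partly removed from the tDCS contrast. The planned difference is just 2 points, so it is worth checking how large either effect could be. Significance tests of baseline balance do not help: under proper randomisation any difference is due to chance, and a p-value does not show how far the outcome contrast is affected.

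**Working it through.** **Inputs from the documents** (Sample size and power calculations, unless noted)
- Test: "using a two-tailed independent samples t-test having an alpha level of 0.05".
- Difference and SD: "an estimated average difference in FMA gain between both groups of 2 points (SD = 3", so d = 2/3 = 0.667.
- Stated result: "with an effect size of 0.66 and a power of 85%, we calculated that a total of 84 participants will be needed".
- Attrition: "presuming an attrition rate of 20%, a total of 105 participants will be recruited".
- Allocation 1:1 (Randomisation and blinding), so 42 per arm.

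**Step 1: the plan's own figures.** Two-sided two-sample t-test, noncentral t:
- d = 2/3 needs 42 per arm, 84 in total; power at 84 is 85.5%.
- The printed d = 0.66 gives 84.8% at 84, which agrees to rounding.
- 84 / (1 − 0.20) = 105.

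The sample size reproduces without any covariate.

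**Step 2: gain in power from adding baseline FMA.** Let c be the size of the correlation between baseline FMA and FMA change that remains after MEP stratum. The documents do not give c, so it is an assumption. The SD of 3 is kept as the unadjusted SD. The residual variance is multiplied by 1 − c², so the effective d is 0.667 / √(1 − c²). The model has 6 cell means and 1 slope, leaving 84 − 7 = 77 residual degrees of freedom.

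| c | 1 − c² | effective d | power, 42 per arm |
|---|---|---|---|
| no covariate | 1.00 | 0.667 | 85.5% |
| 0.1 | 0.99 | 0.670 | 85.8% |
| 0.2 | 0.96 | 0.680 | 86.8% |
| 0.3 | 0.91 | 0.699 | 88.5% |

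A site term takes 2 more degrees of freedom (75 left) and lowers these powers by less than 0.1 percentage point.

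**Step 3: effect of a chance imbalance.** The slope of change on baseline has size c × 3 / SD(baseline). The standard error of the baseline difference is SD(baseline) × √(2/42). SD(baseline) cancels in the product, so an imbalance of 1.96 standard errors moves the unadjusted contrast by

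1.96 × c × 3 × √(2/42) = 1.283 × c.

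- c = 0.1: 0.13 points
- c = 0.2: 0.26 points
- c = 0.3: 0.38 points

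Against the 2-point target these are about 6%, 13% and 19%. An imbalance this large or larger, in either direction, occurs in about 1 trial in 20.

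**Step 4: which values of c are plausible.** If baseline and post-training FMA have equal variances, c = SD(change) / (2 × SD(baseline)), so SD(baseline) = 3 / (2c).

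- c = 0.1: baseline SD 15
- c = 0.2: baseline SD 7.5
- c = 0.3: baseline SD 5
- c = 0.4: baseline SD 3.75
- c = 0.5: baseline SD 3

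With no FMA limits at entry, a baseline SD of 3 to 4 points on a 66-point scale would be narrow. Correlations of 0.1 to 0.3 are therefore the more reasonable range.

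**The case against.** The strongest reply is that nothing here is an error. Randomisation makes the change-score contrast unbiased, the trial reaches its stated power without a covariate, and the change score already subtracts baseline with slope 1. MEP stratum is both a randomisation factor and a model factor, and the article itself links absent MEPs to limited voluntary movement, so part of baseline severity is already balanced and adjusted. All of this stands, and it is why the effect is small.

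A reader might infer more than the documents support in four ways:

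- **That the tDCS comparison is biased, or that baseline imbalance is left wholly uncorrected.** It is unbiased over randomisations, and only the part of an imbalance not removed by subtraction and stratum remains.
- **That adjustment would lift power to 91–94%.** That needs c of 0.4 to 0.5 and hence, under equal variances, a baseline SD of about 3 to 4 points.
- **That site or trainer is unbalanced by design.** The article describes allocation within MEP strata and does not say whether lists are also held by site. A condensed article may leave that to the full protocol.
- **That the baseline tests damage the result.** No action follows from them, so they change no stated analysis. The risk is only that a significant test later prompts unplanned adjustment.

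Two further limits apply. The documents do not show how many participants start near the ceiling, and a linear baseline term would not remove a ceiling effect. An unseen analysis plan might add covariates, but the model is written out in the article, so such a change would need to be reconciled with it.

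**Conclusion.** The point holds as a low-cost improvement. The stated analysis is valid, and the figures of 84, 85% and 105 are sound. By omitting baseline FMA the plan gives up roughly 0.3 to 3 percentage points of power and leaves in the estimate about 0.13 to 0.38 points of an unusually large chance imbalance.

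These sizes rest on an assumed baseline–change correlation of 0.1 to 0.3 after stratum, the planned SD of 3, full data on 42 per arm, and a linear relation. Near 0.1 the gain is negligible; at 0.3 it is worth having.

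**What to change.** Before unblinding, by a dated amendment, prespecify an ANCOVA of FMA change on tDCS group, MEP stratum, their interaction and baseline FMA. Using post-training FMA as the response gives the same tDCS estimate, so the stated outcome need not change. Use the same form for the secondary outcomes, each with its own baseline. A site term may be added.

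Present baseline characteristics by arm descriptively, and state that covariates are fixed in advance and not chosen from baseline significance tests.

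The TMS measures go through the same ANOVA but need separate thought, because baseline MEP amplitude defines the strata.

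Cost: wording and an amendment, with no new data or visits. Baseline FMA uses 1 residual degree of freedom, and site would use 2 more.

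### The follow-up to a tDCS-by-stratum interaction names paired t-tests, but real and sham tDCS are independent groups, so the test cannot show where they differ

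*Protocol article*

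**What the plan says.** The Statistical analysis section of the protocol article analyses change in FMA and in the MEP measures with a two-way ANOVA whose factors are "MEP strata (three levels) and type of tDCS (2 levels". It adds that "The significance level will be set at 0.05". For the next step, should an interaction appear, it says that "paired *t*-tests will be used to locate any significant differences in each stratum with a Bonferroni correction for multiple tests (adjusted *p*-value of 0.02".

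The Randomisation and blinding section fixes the structure of the data: "Within each stratum, participants will be further randomly allocated into two tDCS groups", and "Participants will be randomly assigned to either the tDCS real group or the tDCS sham group with a 1:1 allocation". Allocation uses "blocked randomisation with variable block sizes of 2 and 4". No matching of a real-tDCS participant to a sham participant is described.

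Two other places treat the tDCS arms as independent. The sample size section powers the real-versus-sham difference in FMA gain with a two-tailed independent-samples t-test. The Statistical analysis section itself compares the two arms at baseline with independent t-tests.

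**The concern.** Both ANOVA factors are between-participant factors, the outcome is already a change score, and there is no time factor. An interaction in this model therefore means one thing: the real-minus-sham difference in change is not the same in all three MEP strata. Locating it means comparing two independent groups within each stratum.

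A paired t-test cannot do that. The only pairing the design supplies is a participant's own baseline and post-training score, and a test on those pairs asks whether participants improved. The protocol expects every stratum to improve in both arms, so the answer would be yes throughout.

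At stake is any statement about which strata benefit from tDCS. The added benefit of tDCS is the secondary aim and the basis of the sample size. An analyst who followed the sentence could report strata as positive when stimulation did nothing there. Changing the test after an interaction had been seen would look data-driven.

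**Working it through.** **Inputs.** From the sample size section: expected FMA gain of at least 6 points (sham) and 8 points (real), difference 2, SD 3, effect size 0.66, two-sided alpha 0.05, power 85%, N = 84, and 105 recruited after 20% attrition. From the Statistical analysis section: three strata, two tDCS types, cut-off 0.02. Assumptions: equal strata, so 84/6 = 14 per arm and 28 per stratum (the protocol gives no stratum sizes), and SD 3 taken as the SD of an individual's gain, as the effect size 2/3 implies.

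**1. The plan's own sample size.** The two-sided independent-samples t-test with d = 2/3 and 85% power needs 41.4 per arm, rounded up to 42, so 84 in total. Attrition: 84/0.8 = 105. Both figures reproduce, and they rest on an independent-groups test of the contrast that the follow-up is meant to examine.

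**2. The paired test read literally.** Take a stratum where tDCS has no effect and both arms gain 6 points. With t = mean gain / (SD/√n):
- whole stratum, n = 28: 6/(3/√28) = 10.6, against a two-sided 0.02 critical value of 2.47 (27 df);
- one arm, n = 14: 6/(3/√14) = 7.5, against 2.65 (13 df).

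Power at 0.02 exceeds 99.99% in both cases. If the SD of gain is doubled to 6, it is still 99.6% (n = 28) and 84% (n = 14).

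**3. Paired and independent tests side by side.** Simulated trials, 14 per arm per stratum, sham gain 6, SD 3, and illustrative tDCS effects of 0, 0 and 4 points in the three strata. Tests are at 0.0167, taken without regard to the interaction gate:

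| Follow-up test | Stratum 1 (effect 0) | Stratum 2 (effect 0) | Stratum 3 (effect 4) |
|---|---|---|---|
| Paired pre-post, n = 28 | 100% | 100% | 100% |
| Independent real v sham | 1.7% | 1.7% | about 83% |

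The paired test does not distinguish the three strata. The independent test does.

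**4. The cut-off.** 0.05/3 = 0.0167, which rounds to 0.02 at two decimals. Other candidates do not give 0.02: 0.05/2 = 0.025, 0.05/6 = 0.0083, Šidák for three tests 0.0170.

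The follow-up runs only after an interaction at 0.05, so family-wise error for three real-versus-sham tests on one outcome is bounded as follows:
- no tDCS effect in any stratum: there is no true interaction, so the gate opens in 5% of trials and error cannot exceed 5%;
- the same non-zero effect in every stratum: no stratum hypothesis is null, so no false positive is possible;
- a true interaction: at most two strata can be null, so error is at most 2 × 0.02 = 0.04.

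Simulation of the gated procedure with independent tests at 0.02 (100,000 trials each) gave 2.5% for effects 0/0/0, 3.1% for 0/0/4 and 4.0% for 0/0/8.

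**The case against.** The best defence is that paired was written for pairwise. The authors use independent t-tests for the same two arms at baseline and in the sample size section, so they know the arms are separate people. That is plausible. It makes the repair trivial but does not remove the need for it. The protocol uses both terms, and an analyst cannot be expected to read one as the other.

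A second defence is that pre-post tests have a purpose: the stated primary goal is whether the training programme improves arm function. That stands in part. Such tests describe change within a stratum, but they do not follow up an interaction with tDCS. They answer a different question.

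Third, the claim that everything would be significant is shown only for FMA. The protocol states no expected change for MEP amplitude, motor threshold or silent period. This is right, and the size given here is confined to FMA. For the MEP measures the mismatch between test and question remains, without a number.

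Fourth, the step is conditional and its reach is small. This also stands: the tDCS main effect, the interaction test, the randomisation and N = 84 do not depend on it.

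Two stronger readings are tempting and are not supported. A reader might infer from 3 × 0.02 = 0.06 that the cut-off breaches 5%. That ignores the interaction gate, under which the error stays within 5%. A reader might also count six tests, one per stratum and arm, and call the correction far too weak. The protocol says in each stratum, which points to three tests, and nowhere states a family of six.

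**Conclusion.** Wrong as written, and it should be fixed. Real and sham tDCS are independent groups within each stratum, so paired t-tests cannot locate a tDCS-by-stratum interaction. With the protocol's expected FMA gains, an SD of gain of 3 and an assumed 14 per arm per stratum, a pre-post test would be significant in essentially every stratum whether or not tDCS works there. The conclusion that the test does not match the question needs none of these assumptions; only its size does.

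The defect is confined to the conditional follow-up. Writing 0.0167 for 0.02 is a minor precision point: it changes the reading only of p-values between the two figures, and it does not show uncontrolled error.

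**What to change.** Replace the follow-up sentence with wording such as: If the interaction between tDCS type and MEP stratum is significant at 0.05, the difference between real and sham tDCS in mean change will be estimated within each stratum as an independent-groups contrast from the fitted ANOVA, with its 95% confidence interval, and tested at 0.05/3 = 0.0167. Paired pre-post comparisons will be reported as descriptive results only.

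The cost is one sentence, with no change to data collection or sample size. It should be made before any unblinded analysis; the protocol describes recruitment as ongoing.

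The correct test will have limited power. For the planned 2-point difference with SD 3 and 14 per arm, an independent-samples t-test within one stratum has about 23% power at 0.0167 (26% at 0.02). The trial was sized for the overall tDCS difference, so stratum results should be read mainly through their confidence intervals.

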According to the existing literature, there is a clear need to further validate the use of MEPs as a classification tool and to explore new ways on how to refine the use of this measure, in order to optimize post-stroke training interventions. In addition, since tDCS is still relatively new in the field of stroke rehabilitation, no study to date has tried to determine whether tDCS can enhance the effects of a strength training intervention in stroke patients; a type of intervention commonly used in rehabilitation [3]. Ultimately, there is an urgent need to design better training interventions for the management of post-stroke disability, notably by adapting programs to meet each individual’s capacity in terms of potential for recovery. There is also an important need to determine whether non-invasive brain stimulation techniques, such as tDCS, can be used in conjunction with tailored strength training exercises to boost functional recovery after stroke.

The primary goal of this RCT is to determine whether a 4-week tailored strength training program could lead to improved arm function in chronic stroke survivors. The secondary aim is to determine whether combining anodal tDCS of the lesioned hemisphere with strength training could lead to further improvement in arm function when compared to sham tDCS. This study will help determine whether tailored strength training interventions in stroke survivors, based on MEPs amplitude, can lead to greater gains in arm function. In addition, it will also establish whether combining anodal tDCS with tailored strength training can further promote recovery in stroke survivors when compared to sham tDCS.

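### The plan names no estimate of training gain free of active tDCS, and its only pre-post tests, read literally, pool real and sham participants

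*Protocol article*

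**What the plan says.** The Background section of the protocol article separates two aims. The primary goal is to "determine whether a 4-week tailored strength training program could lead to improved arm function in chronic stroke survivors". The secondary aim is to establish whether "combining anodal tDCS of the lesioned hemisphere with strength training could lead to further improvement in arm function when compared to sham tDCS".

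All participants train (Intervention period). Under Randomisation and blinding: "Within each stratum, participants will be further randomly allocated into two tDCS groups". Assignment is to the "tDCS real group or the tDCS sham group with a 1:1 allocation", using "blocked randomisation with variable block sizes of 2 and 4". About half of every stratum therefore trains under active stimulation.

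Statistical analysis gives one model for both aims, a 3×2 ANOVA of change by MEP stratum and tDCS type. If an interaction is noted, paired t-tests "will be used to locate any significant differences in each stratum", with a Bonferroni-adjusted level of 0.02. The section gives no other pre-post test and no estimate restricted to the sham arm.

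Sample size and power calculations expects an 8-point FMA gain with real tDCS. The sham group "will show at least a 6-point gain on the FMA scale", which the section sets against a 5-point MDC. The difference of 2 points (SD 3) leads to 84 participants, or 105 recruited.

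**The concern.** Only the sham arm shows what training does without active tDCS. The sample size section treats it that way, because it derives the expected sham gain from a strength-training result. The analysis section does not carry this through to the primary goal.

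A paired test compares the same people before and after. Applied to a whole stratum, it measures training plus whatever tDCS added in the half that received it. The condition on the test makes this worse. The test is run only when the tDCS effect appears to differ between strata, which is when averaging over arms is hardest to defend. A stratum could then be credited with a training response that belongs partly to stimulation, and strata with the same training response could look different. That bears on the use the Discussion foresees for MEP stratification, namely guiding exercise prescription.

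**Working it through.** **1. The plan's own sample size.** Inputs from Sample size and power calculations: difference 2, SD 3, effect size 0.66, two-sided alpha 0.05, power 85%, 1:1. With d = 2/3, the exact noncentral t calculation gives 42 per arm, 84 in total (power 85.5%). With d rounded to 0.66, the normal approximation also gives 84; the exact calculation gives 86, with power 84.8% at 42 per arm. Attrition: 84 / (1 − 0.20) = 105. The stated figures reproduce.

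**2. What the adjusted level implies.** 0.05 / 3 = 0.0167, which rounds to 0.02. Six tests, one per stratum and arm, would need 0.05 / 6 = 0.0083. So the plan has three tests, one per stratum. This rules out separate pre-post tests by arm. It does not by itself distinguish three pooled pre-post tests from three real-versus-sham contrasts. The word *paired* points to the former.

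**3. Pooled gain.** Let S be the sham-arm gain in a stratum and D the tDCS effect there. Under 1:1 allocation:

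pooled gain = ½·S + ½·(S + D) = S + D/2.

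With the plan's overall figures, S = 6 and D = 8 − 6 = 2, so the pooled gain is 7. The excess is 1 point, and 1/6 = 17% of the training gain.

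**4. Differences between strata.** For strata j and k, the difference in pooled means is (S_j − S_k) + (D_j − D_k)/2. If D is common to all strata the second term is zero, so the ANOVA stratum term is not biased. If D differs, it is not zero. As an illustration, D = 4 in one stratum and 0 in another makes the pooled means differ by 2 points when the training gains are identical.

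**5. Effect on the pooled paired test (illustration).** Assume 28 per stratum (84 in equal strata; the protocol does not give stratum sizes), half on real tDCS, SD 3, normal data and a true training gain of zero. In 20,000 simulated trials per row, the chance of a significant positive result at 0.02 is:

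| tDCS effect in the stratum | Significant gain |
|---|---|
| 0 | 1.0% |
| 2 | 22% |
| 3 | 47% |
| 4 | 70% |

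**6. Precision of a sham-only estimate** (SD 3, 84 participants, equal strata).

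- Overall: 3/√42 = 0.46 against 3/√84 = 0.33.
- Per stratum: 3/√14 = 0.80 against 3/√28 = 0.57.

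The ratio is √2 in both cases, so the standard error is about 41% larger.

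**The case against.** **Pooling is nowhere stated in words.** This is correct. The natural follow-up to a stratum-by-tDCS interaction is real versus sham within each stratum, and three such contrasts fit 0.02 equally well. On that reading no pooling occurs. But the arms contain different people, so a paired test cannot make that comparison, and the section then contains no pre-post test for the primary goal at all. The wording needs correcting on either reading.

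**The ANOVA already contains tDCS as a factor.** This also stands in part. The stratum term compares strata, and a common tDCS effect cancels from it. A reader might infer that every training result in the plan is inflated. The documents do not support that; the bias concerns the size of a pre-post gain taken over both arms.

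**The MDC.** A reader might also infer that pooled gains are to be judged against the 5-point MDC, so that a stratum below it could appear above it. No section says so. The MDC appears only in the sample size section, where it is applied to the sham group. A crossing can be constructed. If a share p of participants has no MEP, the plan's gains of 7 (MEP present) and 6 (whole sham group, taking the stated minimum as exact) imply a sham gain of 7 − 1/p in that stratum. With D = 2 the pooled gain is 8 − 1/p. At p = 1/5 these are 2 and 3; at 1/3, 4 and 5; at 1/2, 5 and 6. The two values fall on different sides of the MDC only for shares from one third up to one half, and the protocol gives no share. This is no basis for a finding.

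**Reporting of cell means can be left to a SAP.** This is true of reporting detail. Here the article itself fixes the test, its unit and its level, and as written that rule yields a biased training gain.

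**A sham-only estimate is still uncontrolled.** This is correct. Everyone trains, so the sham-arm change remains a before-after change. The lack of an untrained or untailored comparator is a separate issue that this point does not resolve.

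**Conclusion.** The point holds in a limited form. Statistical analysis names no training-gain estimate free of active tDCS, although training is the primary goal. Its conditional paired tests, taken literally, measure training gain plus half of each stratum's tDCS effect. On the plan's own expectations that is 7 points against 6 overall. At those values the sham gain of 6 already exceeds the 5-point MDC, so the headline conclusion would stand. Within a stratum the excess is half of whatever the tDCS effect is there, and the documents give no stratum-specific figure.

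The result rests on 1:1 allocation within strata, which is stated, and on reading the paired tests as pooled over arms, which is inferred. If that inference is wrong, the named test is wrong for the comparison intended. The real-versus-sham comparison and the sample size are unaffected.

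**What to change.** In Statistical analysis:

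- Define the training gain as the sham-arm mean change with a 95% CI, overall and by stratum, taken from the planned 3×2 model. State how strata are weighted in the overall figure.
- Report the real-arm gain with its CI, labelled as training plus tDCS.
- Replace the paired tests after an interaction by real-versus-sham contrasts within each stratum (independent samples, or the corresponding model contrasts), at 0.05/3 = 0.0167.
- State that pre-post change pooled over arms will not be presented as a training effect, and that the sham-arm gain is an uncontrolled before-after change.

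No new data or participants are needed, since the cells are already in the model. The price is the wider interval for training gain shown above, most noticeable per stratum (0.80 against 0.57), and wider still in any stratum that recruits fewer than an equal share.
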